## Sample Size Determination

Sample size calculations were performed using Open-Epi version 3.1, based on the following assumptions: a 99% confidence level, 80% power, an exposed-to-unexposed ratio of 1, a POP-SS mean difference of 3.16 with a standard deviation of 4.78 in the intervention group, and a mean difference of 0.12 with a standard deviation of 3.86 in the control group over six months (14). Considering a 16% (15) refusal and loss to follow-up, the effective sample size (individual-based randomization) is 113.4. The decision to adjust the confidence level to 99% was based on the adjusted level of significance to 0.0125 than the usual p-value of 0.05 to account for multiple comparisons across various outcomes (16) (POP-SS and three distinct domains of P-QoL).

The minimum number of clusters needed is calculated by multiplying the effective sample size by the Intra-Cluster Correlation Coefficient (ICC) factors for both groups (17). The estimated fairly typical value of the Intra-Cluster Correlation (ICC) factor is 0.03 (17-19). Accordingly, the minimum required cluster number is 1.67 for each group (intervention and control group). However, to ensure the adequacy of the cluster and to have good power (20, 21), eight clusters (kebeles) will be included in this study. To account for the cluster effect, the effective sample size is multiplied by a Variance Inflation Factor (VIF) of 1.35. The Variance Inflation Factor (VIF) is calculated with the assumption of an equal cluster size. Using Intra-Cluster Correlation value of 0.03, (VIF = 1+ ((n-1) ICC)), where ‘n’ is the average cluster size (17-19). Accordingly, the adjusted sample size is 155 with 19.4 participants per cluster.

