## Data Measurements

At each visit, women's adherence to pelvic floor muscle training will be evaluated by their pelvic muscle trainer. At week two, women will be assessed for adherence to pelvic floor muscle exercise in the last two weeks (three times a day, once a day, a more than once per week, once per week, a more than one days per week). At weeks six, 10, and 15, they will be assessed for adherence to pelvic floor muscle exercise in the last four weeks using similar questions used on week two (three times a day, once a day, a more than once per week, once per week, a more than one day per week). In addition, they will be assessed for prolapse symptoms at weeks 10 and 15.

At the end of six months, the overall adherence to training protocol will be evaluated from their dairy or report of pelvic muscle trainer. Women’s adherence to training protocol is considered adequate when they complete at least 80% of the training sessions (24). This will be calculated at each visit based on the training session and finally compiled.

The primary outcome of the study is a change in prolapse symptoms measured by POP-SS. The POP-SS is the same measurement with study one which measures the frequency of prolapse symptoms in the last four weeks, measured by seven items with a Likert-scale of 0 to 4 scale (0= never felt symptom, 1= occasionally, 2= sometimes, 3= most of the time and 4= all of the time). The total score will be calculated by summing up all responses for the seven-question and the total score will range from 0 to 28, the highest value indicating the severity of prolapse symptoms (25, 26). At the end of the six months, the mean change in prolapse symptoms from the initial visit will be compared between the two groups (intervention and control groups) to measure the effect of pelvic muscle training.

The secondary outcome, women’s perceived change in prolapse symptom since the start of the intervention, will be measured as improved, the same, or worsened based on Patient Global Impression of Change (PGIC) (14, 27).

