## Data Management and Analysis

Data entry, cleaning, missing data management and descriptive data presentation is similar with Paper-II. In addition, in this paper, to assess the effect of pelvic floor muscle training on prolapse symptoms, an Intention-to-treat (ITT) analysis will be used at the end of six months of training. This analysis will include all women included in the trial study at the beginning and who attended at least one follow-up. A paired t-test will be used to evaluate the mean change from baseline for both groups (intervention and control) groups. Then independent t-test will be used to compare the mean change for the interventional groups against the mean change of the control group as an effect size. The level of significance will be set at a P-value < 0.0125 by using the Bonferroni correction formula for multiple outcomes (16, 29, 30). In this study, there are four outcomes of this single intervention, which included a mean change in prolapse symptoms and three components of prolapse quality of life (Paper IV). Therefore, the level of significance is obtained by dividing the usual P-value (0.05) by a number of statistics to be performed.

A summary of statistics will be computed both at the cluster-level and individual levels for both arms. The presence of cluster effects will be assessed and a multilevel analysis will be considered if a significant ICC value of > 0.5 is detected (31). As an alternative, since the outcome of this study is continuous data, both the cluster-level and individual-level analysis will produce the same result if the cluster size is equal. But if the cluster size is variable, an individual-level analysis weighted by cluster size will be done (20, 21).

This study will use stratified cluster randomization based on geographical locations. This may not balance all possible confounders, especially individual-level factors that may vary across strata. Therefore, the statistical technique of confounder control will be used to control possible confounders at the analysis stage. A Linear Mixed-Effect Model will be used to control confounders in multivariable linear regression. This analysis can increase the statistical power and preferable than the general equation estimation model (GEE) (32). Multicollinarity of the independent variables will be checked before fitting the variable into multivariable linear regression in similar fashion with Paper-II.

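### The test carrying the effect size and the 0.0125 threshold is an unadjusted t-test on change; no analysis is named confirmatory and the mixed model's baseline term is undefined

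*Protocol*

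**What the plan says.** Paper-III (Data Measurements) states: "The primary outcome of the study is a change in prolapse symptoms measured by POP-SS". Its Data Management and Analysis section first plans paired t-tests within each arm. It continues: "Then independent t-test will be used to compare the mean change for the interventional groups against the mean change of the control group", and calls the result the effect size. The threshold follows directly: "The level of significance will be set at a P-value < 0.0125 by using the Bonferroni correction formula for multiple outcomes". The family is defined there as well: "there are four outcomes of this single intervention, which included a mean change in prolapse symptoms and three components of prolapse quality of life". Paper-IV repeats the t-test and the threshold for each P-QoL component. The Summary also names the t-test as the between-group evaluation.

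The same Paper-III section, and the Summary for both outcomes, plan a Linear Mixed-Effect Model to control confounders, and Paper-III remarks that it can raise power. The Variables sections of Papers III and IV list its candidate covariates, roughly twenty in each. Both lists contain POP-SS severity and adherence to the training protocol. Separately, a multilevel analysis is considered only if a significant ICC above 0.5 is found.

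**The concern.** Baseline POP-SS and P-QoL are collected from the trial's women, but the comparison tied to the effect size and the significance rule uses them only by subtraction. Two features of this trial make that costly.

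- There are four kebeles per arm, so chance baseline imbalance is likely. The protocol itself accepts that stratification may not balance everything.
- Any non-zero POP-SS counts as symptomatic and eligibility sets no higher cut-off, so a woman's possible improvement is capped by her starting score. Regression on baseline handles imbalance and regression to the mean better than a raw change score does.

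The mixed model does not settle the matter as written. If it and the t-test disagree, the protocol gives no rule for which one decides. With about twenty candidate covariates and a loosely defined baseline term, the adjusted estimate is not fixed in advance either.

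**Working it through.** **1. The plan's own figures.** Sample Size Determination sets "a 99% confidence level, 80% power, an exposed-to-unexposed ratio of 1". Its assumption for the trained women is "a POP-SS mean difference of 3.16 with a standard deviation of 4.78 in the intervention group"; for controls the assumed change is 0.12 (SD 3.86).

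- Difference: 3.16 − 0.12 = 3.04. Sum of variances: 4.78² + 3.86² = 37.75.
- n per arm = 37.75 × (2.576 + 0.842)² / 3.04² = 47.7.
- Total with 16% loss: 2 × 47.7 / 0.84 = 113.6, against the stated 113.4.
- 113.4 × 1.35 = 153.1, against the stated 155.
- 0.05 / 4 = 0.0125, exact. The sizing alpha of 0.01 is slightly stricter.

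The figures reproduce closely, and the trial is sized on change-score SDs.

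**2. The two analyses side by side.**

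- *t-test on change:* has the effect size and the 0.0125 rule attached; no covariate; no kebele term.
- *Mixed model:* no significance rule attached. POP-SS severity is not defined as the continuous baseline total. Adherence is recorded at weeks 2 to 15, after randomisation, and concerns training that only the intervention arm receives. For P-QoL the list has POP-SS severity but not the component's own baseline.

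**3. Gain from adjusting for baseline.** Assume equal SD s at baseline and six months, with correlation r. The change-score variance is 2s²(1 − r) and the baseline-adjusted variance is s²(1 − r²), so the ratio is (1 + r)/2. The documents do not give r; 0.3, 0.5 and 0.7 give ratios of 0.65, 0.75 and 0.85.

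**4. Power of an analysis that respects the kebeles.** Two-sided 0.0125 is assumed, since sidedness is not stated.

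- Analysed: 155 × 0.84 = 130.2, or 65.1 per arm and 16.3 per kebele.
- Design effect: 1 + (16.3 − 1) × 0.03 = 1.46.
- SE of the difference: √(37.75 × 1.458 / 65.1) = 0.920. Noncentrality: 3.04 / 0.920 = 3.31.
- Degrees of freedom: 8 − 2 = 6. Critical t: 3.52.

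| Analysis | Variance ratio | Power, about 130 analysed | Power, all 155 analysed |
|---|---|---|---|
| Change score | 1 | 49% | 54% |
| Baseline-adjusted, r = 0.3 | 0.65 | 70% | 75% |
| Baseline-adjusted, r = 0.5 | 0.75 | 63% | 69% |
| Baseline-adjusted, r = 0.7 | 0.85 | 57% | 62% |

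The last column (SE 0.869) shows what the figures would be without the plan's own 16% loss.

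**5. Why clustering must be fixed at the same time.** If the t-test ignores an ICC of 0.03, its true two-sided error at nominal 0.0125 is about 2 × P(Z > 2.498 / √1.46) = 3.9%. Extra precision without a kebele term would sharpen an anti-conservative test.

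**6. Holm against Bonferroni.** Simulated POP-SS power for four correlated z-statistics, with an assumed outcome correlation of 0.5 and noncentralities of 2.5, 3.0 and 3.3:

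| P-QoL effects | Bonferroni to Holm |
|---|---|
| As large as POP-SS | 50 to 59%, 69 to 78%, 79 to 87% |
| Half as large | 50 to 51%, 69 to 70%, 79 to 79% (gains of about 1 point) |
| None | no change beyond 0.1 point |

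Holm's first step is also 0.0125, so POP-SS gains only when another outcome has been rejected first.

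**The case against.** A reader might infer that the plan throws the baseline scores away, or that it declares the t-test confirmatory. The text supports neither. A mixed model listing POP-SS severity is planned for both papers, and its place after the t-test is only paragraph order. The supportable defects are the unstated hierarchy and the badly fixed covariates.

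A reader might also call Bonferroni, or the change score, an error. Under randomisation a change score is unbiased, and 0.05/4 controls family-wise error. Both are choices about efficiency.

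Nor is 49% the power of the planned test. It belongs to a cluster-respecting analysis on 6 df, whereas the planned t-test is at the individual level.

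The gains are conditional. The correlation r is an assumption. Equal SDs are doubtful given the floor on improvement and the unequal change SDs. The calculation also lets kebele-level variance shrink in the same proportion as individual variance. For Holm, Paper-IV says the effect on P-QoL could not be determined, so nothing supports counting on the equal-effects case.

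Detailed covariate specification can often be left to an analysis plan. That does not cover this case: the protocol itself attaches the effect size and threshold to the unadjusted test, and itself puts adherence in both covariate lists.

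**Conclusion.** The point holds in limited form. The comparison carrying the effect size and the 0.0125 threshold is an unadjusted individual-level t-test on change. The alternative model is planned but not ranked, and its baseline adjustment is inadequately defined: POP-SS severity is unspecified, baseline P-QoL is absent, and a post-randomisation variable is included.

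Naming one baseline-adjusted, cluster-respecting model as primary is worth about 8 to 21 percentage points of power (49% to between 57% and 70%) under the stated assumptions. With equal SDs the gain is positive for every r below 1, but it shrinks as r rises, to about 54% power at r = 0.8. Holm is a valid optional improvement whose benefit for POP-SS may be essentially nil.

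**What to change.** 1. For POP-SS and for each P-QoL component, name as primary a model of the six-month score on arm and the same score at baseline (continuous), with a random kebele intercept and small-sample degrees of freedom. Use it whatever ICC is observed, in place of the ICC > 0.5 condition. State that its arm coefficient is the effect size and that its p-value is the one tested.
2. Keep the many-covariate model as a sensitivity analysis, with adherence removed. Keep the paired t-tests as description only.
3. Optionally, replace the fixed 0.0125 with Holm over the four p-values (0.0125, 0.0167, 0.025, 0.05). Family-wise error is unchanged and it never rejects less.

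Items 1 and 2 are changes of wording, with no extra women, visits or measurements. Holm has two costs: its confidence intervals are less simple than Bonferroni intervals, and the Paper-III and Paper-IV p-values must be ranked together before either paper states its conclusions.

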**Methods:** This study will be conducted in two phases. Initially, the pelvic organ prolapse Symptom Score questionnaire will be translated into Sidaamu Afoo and evaluated for its psychometric properties on a sample of 70 women with pelvic organ prolapse recruited from the gynecology outpatients of Adare General Hospital and Yirgalem Hamline Fistula Center from May 1-25, 2022. Then a complex sample survey will be conducted to establish the prevalence of prolapse based on a sample size of 816 women. It will be conducted in eight kebeles of the Dale and the Wonsho districts from June 1–July 30, 2022. A multistage stratified sampling technique will be used to recruit study participants. The data will be collected through face-to-face interviews with the selected women at the household level. Then all women will be invited to have a pelvic examination at a nearby health facility where the prevalence of the prolapse will be determined by pelvic examination. A complex sample survey analysis will be used to determine the prevalence and determinants of pelvic organ prolapse. In the second phase of the project, a cluster-randomized controlled trial study will be conducted to evaluate the effect of pelvic floor muscle training for the reduction of prolapse symptoms and improving quality of life among 136 (68 participants in each arm). The health-related quality of life will be assessed by using a translated Sidaamu Afoo version of the Prolapse Quality of Life tool, validated in the Amharic version. A Student t-test will be used to evaluate the mean change between the two groups (control and intervention), both for prolapse symptoms and quality of life separately. Linear Mixed-effect Model will be used to control potential confounders in multivariable linear regression for both outcomes.

**Work Plan and Budget**: This study will be conducted from April to November 2022. A total of **762, 295** Ethiopian Birr **($15,245.9)** is needed to conduct this study.

**Key terms:** Ethiopia, Pelvic Organ Prolapse, prolapse, POP, quality of life, pelvic floor muscle exercise, PFMT, pelvic muscle training

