## Data Management and Analysis

The Data management and analysis procedure is similar with paper-III. In addition to that, a paired t-test will be used to evaluate the mean change of the three components of P-QoL from baseline for both groups (intervention and control) groups. Then an independent t-test will be used to compare the mean change for interventional groups against the mean change of the control group as the effect size for all the three components separately. The level of significance will be set at a P-value < 0.0125 by using the Bonferroni correction formula for multiple outcomes (16, 29, 30).

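### Kebeles are randomised, but the arms are compared by an individual-level t-test at 0.0125; the ICC > 0.5 gate to a multilevel analysis is practically unreachable and the planned mixed model does not clearly close the gap

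*Protocol*

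**What the plan says.** Paper III, Data Management and Analysis, sets the between-arm comparison of POP-SS change: "Then independent t-test will be used to compare the mean change for the interventional groups against the mean change of the control group". The next sentence attaches the error rate: "The level of significance will be set at a P-value < 0.0125 by using the Bonferroni correction formula for multiple outcomes". Paper IV, Data Management and Analysis, repeats both steps for the three P-QoL components ("Then an independent t-test will be used to compare the mean change for interventional groups against the mean change of the control group"), and the Summary names a Student t-test for both outcomes. None of these places attaches a cluster term to the test.

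The same Paper III section then deals with clustering in three steps:

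- a gate: "a multilevel analysis will be considered if a significant ICC value of > 0.5 is detected";
- a justification: "both the cluster-level and individual-level analysis will produce the same result if the cluster size is equal";
- a fallback for unequal cluster sizes: "an individual-level analysis weighted by cluster size will be done".

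It finally plans a linear mixed-effect model without condition, to adjust for confounders that the stratified allocation may leave unbalanced. No random effect is named.

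Paper III, Sample Size Determination, takes clustering seriously: "The estimated fairly typical value of the Intra-Cluster Correlation (ICC) factor is 0.03". It inflates 113.4 women to 155 in eight kebeles.

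**The concern.** The sample size treats women in one kebele as correlated. The analysis then treats them as independent unless that correlation is about 17 times larger than planned (0.5/0.03 = 16.7), and even then a multilevel analysis is only to be considered.

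If kebeles differ for reasons unrelated to the training, the naive standard error is too small. Intervals for POP-SS and the three P-QoL components would be too narrow, and the Bonferroni level of 0.0125 would not hold. A difference between four kebeles and four others could then be reported as an effect of the training.

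**Working it through.** **Inputs.** From Paper III, Sample Size Determination: 8 kebeles, 155 women, 19.4 per kebele, ICC 0.03, inflation factor 1.35, 16% loss, mean changes 3.16 (SD 4.78) and 0.12 (SD 3.86). From the flow diagram: 4 kebeles per arm. From Paper III, Data Management and Analysis: level 0.0125. The protocol does not state sidedness; two-sided is assumed.

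**The plan's own figures.** 0.05/4 = 0.0125, as stated. Before clustering, at the 99% level and 80% power, (4.78² + 3.86²)(2.576 + 0.842)²/3.04² = 47.7 per arm. Then 2 × 47.7/0.84 = 113.6, against the stated 113.4. With clustering, 113.4 × 1.35 = 153.1, against the stated 155. These reproduce closely.

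**True level of the t-test.** The design effect is DE = 1 + (m − 1) × ICC. The true level of a nominal 0.0125 test that ignores it is 2[1 − Φ(2.498/√DE)].

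| Setting, ICC 0.03 | DE | True level | Multiple of 0.0125 |
|---|---|---|---|
| Protocol's factor | 1.35 | 0.032 | 2.5 |
| m = 155 × 0.84/8 ≈ 16.3, after loss | 1.46 | 0.039 | 3.1 |
| m = 19.4, no loss | 1.55 | 0.045 | 3.6 |

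Simulation (20,000 trials per setting, 4 + 4 kebeles, normal data, no effect) gives 0.036 at 16 women per kebele and 0.043 at 19. A t-test on the eight kebele means, with 6 df, stays at 0.012 to 0.013.

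**Dependence on where the ICC lies.** Kebeles are allocated within location strata. From the flow diagram I took 2 + 2 Dale-rural, 1 + 1 Wonsho-rural and 1 + 1 urban. If half of the ICC of 0.03 lies between these strata, the simulated level is 0.024 to 0.025; with four location effects shared between arms it is 0.027. Both are about twice nominal. If all of it lies between strata, the level is 0.012 to 0.013, so there is no inflation.

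**Dependence on the ICC (assumed values).** With all variation within strata, ICC 0.01 gives 0.020 to 0.022 and ICC 0.05 gives 0.060 to 0.072.

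**The gate.** At a true ICC of 0.03 the estimated ICC exceeded 0.5 in 0 of 20,000 trials per setting, with a largest value of about 0.32 when all variation was within strata. It also never did so at a true ICC of 0.10. At 0.30 it did in about 5% of trials. An ICC just below 0.5 would leave the t-test standing with DE = 1 + 18.4 × 0.5 = 10.2 and a true level of about 0.43.

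**The equivalence sentence.** With equal cluster sizes the two analyses share the point estimate. At m = 19.4 and ICC 0.03 the correct standard error is √1.55 = 1.25 times the naive one. The degrees of freedom are 8 − 2 = 6 against 155 − 2 = 153.

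**Power of a valid test.** The mean variance is (4.78² + 3.86²)/2 = 18.87. The standard error of the difference in arm means is √(2 × 18.87 × DE/(4m)), which is 0.919 at m = 16.3 and 0.869 at m = 19.4. The non-centrality is 3.04/0.919 = 3.31 or 3.04/0.869 = 3.50. The two-sided 0.0125 critical value on 6 df is 3.52. Power is 49% or 54%.

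**The case against.** The strongest reply is the mixed model. The protocol plans it unconditionally, in Paper III and in the Summary for both outcomes, and prefers it to GEE. It never calls the t-test confirmatory and describes that comparison as an effect size. So a reader might infer that clustering is ignored altogether below the gate; the documents do not support that. What stands is narrower. The significance level directly follows the t-test, the model's only stated role is confounder control, and no kebele random intercept is named. If the model were the primary cluster analysis, the gate would have no purpose.

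A reader might also infer that the false-positive rate is three times nominal as a matter of fact. It is conditional. The protocol offers 0.03 only as a typical value and does not divide it into between-strata and within-strata parts.

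The equivalence sentence is defensible if the individual-level analysis meant is a random-intercept model: with equal sizes and no covariates, that reproduces the comparison of kebele means whenever the estimated between-kebele variance is positive. It fails for the naive t-test that the section actually names. The weighting sentence may be a garbled reference to weighted kebele means. As written, it gives no variance correction.

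The 0.5 may be a slip. The document does not show for what, and eight clusters estimate an ICC too imprecisely for a lower threshold to be a sound gate.

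**Conclusion.** The point holds. As written, the test tied to P < 0.0125 does not match the unit of randomisation, and the condition for moving to a multilevel analysis would practically never be met at the planning ICC. The planned mixed model conflicts with that condition and does not clearly take over the inference.

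At ICC 0.03 the size of the problem is a true level of about 0.036 to 0.045 if the variation lies within strata, about twice nominal if half lies between the balanced strata, and none if all does. This rests on eight kebeles, 16 to 19 women in each, two-sided testing and approximate normality. Paper III's Study Design calls the clusters enumeration areas, whereas the sample size and randomisation sections use kebeles. The figures here are for kebeles, but the t-test ignores either unit.

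**What to change.** Delete the ICC > 0.5 trigger. Delete or correct the equivalence and weighting sentences. For POP-SS and each P-QoL component, name one confirmatory analysis, used whatever ICC is observed:

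- a linear mixed model with a random kebele intercept, the randomisation strata and small-sample degrees of freedom (Kenward-Roger or Satterthwaite), with a stated rule for a between-kebele variance estimated as zero, which happened in about 30% of the simulated trials at ICC 0.03; or
- a cluster-level test on the kebele means, saying how the strata enter.

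Keep the individual-level t-test as description, and align the Summary, Paper III and Paper IV.

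The cost is more than wording. Intervals widen, and the 80% power claim must be restated: the unstratified cluster-means test has about 49% to 54%. Fitting three strata leaves 4 df and about 35% to 39% if the strata remove no variance. The number of kebeles should therefore be reconsidered together with the analysis, or the lower power stated openly.

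### The rule for unequal clusters puts a cluster-size weight on individual records, so a kebele of m women counts m squared and precision is lost

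*Protocol*

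**What the plan says.** Paper III, Data Management and Analysis, lists several analyses of the change in POP-SS. Paired t-tests within arms come first, then an independent t-test between arms. Multilevel modelling has a threshold: "a multilevel analysis will be considered if a significant ICC value of > 0.5 is detected". The section then remarks that cluster-level and individual-level analyses agree when clusters are equal, and continues: "But if the cluster size is variable, an individual-level analysis weighted by cluster size will be done (20, 21". For covariates it adds: "A Linear Mixed-Effect Model will be used to control confounders in multivariable linear regression". The test level is fixed: "The level of significance will be set at a P-value < 0.0125".

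Paper IV brings the same rules to the three P-QoL components: "The Data management and analysis procedure is similar with paper-III".

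Paper III, Sample Size Determination, assumes equal clusters and an ICC of 0.03, and ends: "Accordingly, the adjusted sample size is 155 with 19.4 participants per cluster". The trial flow diagram shows four clusters and 78 women per arm.

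**The concern.** A cluster-size weight makes sense when the data are one mean per kebele, because it restores to each mean the number of women behind it. The rule attaches that weight to the individual analysis, where size is already counted once. The result averages neither over women nor over kebeles, and the protocol gives no reason for wanting such an average.

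Three things are at stake: how far one kebele out of four steers its arm's estimate, the precision of the comparison, and the validity of a test whose standard error takes the weights at face value. Through Paper IV the rule reaches all four outcomes that share the corrected significance level.

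**Working it through.** **The plan's own figures.** Inputs from Sample Size Determination: changes of 3.16 (SD 4.78) and 0.12 (SD 3.86), "a 99% confidence level, 80% power, an exposed-to-unexposed ratio of 1", 16% loss, ICC 0.03, inflation factor 1.35.

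- Per arm: (4.78² + 3.86²)(2.576 + 0.842)² / 3.04² = 47.7, so 95.4 in total.
- After loss: 95.4 / 0.84 = 113.6, against 113.4 stated.
- After clustering: 113.4 × 1.35 = 153.1, against 155 stated. The printed formula with n = 113.4/8 = 14.2 gives a factor of 1.395 and N = 158.2. Both are within 3% of 155.
- Per cluster: 155/8 = 19.4. In the flow diagram, 78/4 = 19.5.

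The sample size is therefore reproduced closely. It assumes equal clusters and says nothing about the weights.

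**What the rule does.** Let kebele j have m_j women and mean ȳ_j. With weight m_j on each woman, the arm estimate is

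Σ_j Σ_i m_j y_ij / Σ_j (m_j × m_j) = Σ_j m_j² ȳ_j / Σ_j m_j².

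The unweighted individual analysis gives Σ_j m_j ȳ_j / Σ_j m_j. A numerical check on simulated data agrees: weighted least squares and the m²-weighted mean of kebele means both give 3.2312; ordinary least squares and the m-weighted mean both give 3.4291.

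**Direction.** The most precise weight for a kebele mean is m/(1+(m−1)ICC). For any ICC from 0 to 1 this lies between equal weights and m. Weighting by m² goes beyond m on the far side, so it is less precise than no weighting whenever sizes differ.

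**Size.** In units of the total variance, the variance of an arm mean is Σ w_j² [ICC + (1−ICC)/m_j], with w_j proportional to m_j² (the rule) or m_j (unweighted). Kebele sizes are my assumption; each set sums to 78, and ICC is 0.03.

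| Sizes | CV | Largest kebele's share: unweighted → rule | Variance change |
|---|---|---|---|
| 19/19/20/20 | 0.03 | 25.6% → 26.3% | +0.1% |
| 16/18/20/24 | 0.15 | 31% → 37% | +4% |
| 14/17/21/26 | 0.23 | 33% → 42% | +9% |
| 10/15/23/30 | 0.39 | 38% → 51% | +18% |
| 8/12/22/36 | 0.55 | 46% → 65% | +32% |

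For 10/15/23/30 the bracketed terms are 0.1270, 0.0947, 0.0722 and 0.0623. Unweighted shares 0.128/0.192/0.295/0.385 give 0.02108. The rule's shares 0.057/0.128/0.302/0.513 give 0.02495. The ratio is 1.183, so the standard error rises by about 9% (√1.183 = 1.088).

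**Effect on the test.** I simulated two arms of 10/15/23/30 with no effect, 20,000 runs, and tested at 0.0125 with the usual model-based standard error.

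- ICC 0.03: 7.4% false positives weighted, 5.0% unweighted. Of the excess over 1.25%, 5.0 − 1.25 = 3.75 points come from ignoring clustering and 7.4 − 5.0 = 2.4 points from the weights. Repeat runs put the weights' part at slightly over 2 points.
- ICC 0: 1.8% weighted, 1.2% unweighted.
- With a heteroscedasticity-robust standard error the weights' part shrinks: 6.2% against 5.4% at ICC 0.03.

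**The case against.** Four objections carry some weight.

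*The planned design is close to equal.* The survey draws 102 women from every kebele and the sample size assumes equal clusters. The introduction cites a symptom prevalence of 28%. If it applied here, 102 × 0.28 ≈ 29 symptomatic women per kebele, or about 27 after 7% non-response, which is above the 19.5 needed. Near-equal kebeles are therefore feasible, and the loss could be negligible. This stands, and it is why the table starts at 0.1%. It does not remove the point: no quota is stated, women must also have confirmed stage I–III prolapse, yields can differ between kebeles, and 16% refusal and loss is expected.

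*The sentence is one of several analyses.* The section also names an unweighted t-test and a mixed model with no stated weight, and it introduces these remarks as an alternative. This stands. A reader might infer that the trial's only estimate is distorted; the text does not support that. Equally, nothing withdraws the rule. The mixed model is there for confounders, and the multilevel trigger of 0.5 is far above the planning ICC of 0.03.

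*It may be a slip* for a cluster-level analysis weighted by size. That is possible, but the words say individual-level, and an analyst who follows them gets m².

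*The test's error rate is mainly a clustering matter.* Correct. Only the increment shown above belongs to the weights, and it depends on the variance estimator.

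**Conclusion.** The rule is wrong as written and should be corrected. That it gives each kebele weight m² is exact, and the loss of precision relative to no weighting is certain whenever sizes differ. How much is lost depends on sizes the protocol does not give: from about 0.1% to 32% of variance over the assumed range, at ICC 0.03 with four kebeles and 78 women per arm. In the 10/15/23/30 case the weights add about 2.4 percentage points to the false-positive rate of a model-based test; the rest of the excess is a separate matter.

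Three stronger readings are not supported:

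- That the largest kebele dominates. Among the assumed sets it passes half of its arm only at a CV of about 0.4; with mild variation it carries 37% instead of 31%.
- That harm is assured because 155 does not divide by 8. That shows only that sizes cannot be exactly equal at that total. The 136 women named under Description of Intervention would divide into eight groups of 17, and a difference of one woman costs almost nothing.
- That the weights would be entered as frequency weights, multiplying the apparent number of records. The protocol never mentions frequency weights.

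I treat kebeles as the clusters, as the sample size and randomisation sections do. Study Design speaks of enumeration areas; the algebra is the same for either.

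**What to change.** In Paper III, Data Management and Analysis, replace the sentence with wording such as: *If cluster sizes vary, individual-level analyses (the linear mixed model with a kebele random intercept) are run without cluster-size weights; if a cluster-level analysis is reported, kebele means are weighted by m/(1+(m−1)ICC), or equally.* Choose one of the two cluster-level weightings in advance. Apply the same wording in Paper IV, so that its reference back to Paper III does not carry the old rule along.

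If a size-weighted analysis of kebele means was what the authors intended, the correction also makes that plain. The cost is one sentence of analysis text, with no change to data collection, sample size or patient contact.
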